## Abstract

**Introduction:**

Unhealthy weight, especially childhood obesity, is emerging as a growing epidemic and a challenge in developed and developing countries. Partnership with parents to promote healthy lifestyle changes may have a lifelong impact on weight-related outcomes in children. This study aims to determine the efficacy of an Interactive Malaysian Childhood Healthy Lifestyle (*i-MaCHeL*) intervention programme to change weight-related behaviour in preschool child-parent dyads.

**Materials and methods:**

The *i-MaCHeL* programme is a single-blind, theory-driven intervention, two-group cluster randomised controlled trial that evaluates the efficacy of a 3-month health promotion intervention in preschool child-parent dyads. In recognition of the value of multiple theoretical approaches, the strong theoretical basis consists of Social Cognitive Theory, Health Belief Model, and Trans-Theoretical Model principles underpinning the development of the intervention programme. In total, 460 child-parent dyads from 12 preschools in Terengganu, Malaysia, will be recruited. The children in the intervention group will expose to the *i-MaCHeL* classroom activities, while the parents will access the *i-MaCHeL* Web-based educational programme and numerous parent-child home-based online activities. The children in the control group will continue with any existing health-related activities, while the parents will receive the link to the general health newsletters. BMI z-score, dietary intake, physical activity, screen time duration, health-related quality of life, parental self-efficacy, parental role modelling, and parental policies will be assessed at baseline, 3 months’ post-baseline, and at 6 months’ follow-up (9 months’ post-baseline). General linear model repeated measure analysis will be used to determine differences between groups at the 3- and 9-month surveys with adjustment for potential covariates. Statistical analyses will follow intention-to-treat principles.

**Conclusion:**

We hypothesise that the combination of the classroom and interactive Web-based activities will have a strong potential to be effective strategies to sustain child-parent engagement and participation in the weight-related behaviour change programme.

**Clinical trial registration:**

**ClinicalTrials.gov Identifier:**
NCT04711525.

## Introduction

In recent years, the prevalence of unhealthy weight in children has been alarming in many countries. Overall, in World Health Organization European Region, 28.7% of boys and 26.5% of girls (aged 6 to 9 years) were overweight (including obese), and 2.5% and 1.9%, respectively, were thin (COSI 2015–2017) [1]. In Malaysia, overweight and obesity coexist with thinness among children and adolescents. The National Health and Morbidity Surveys (NHMS) previously carried out in 2019 reported that 29.8% of children and adolescents aged 5 to 17 years were classified as either overweight or obese, and another 10% were classified as thin [2]. Furthermore, a growing trend toward the prevalence of childhood obesity has also been seen in Malaysia over the last few decades. The National Health and Morbidity Surveys (NHMS), previously carried out in 2011 and 2015, showed that the prevalence of obesity among children aged 5 to 9 years was increased from 6.7% in 2011 [3] to 14.8% in 2015 [4]. Thus, unhealthy nutritional status, especially childhood obesity, is considered one of the most significant public health issues in Malaysia.

Childhood obesity is a subject matter of priority worldwide. Childhood obesity results in physical and psychological comorbidities, which correlate with the chronicity of diseases that often persist into adulthood [5]. Early childhood-onset obesity is of particular concern because a study has reported that children who had a BMI between the 85th and 95th percentiles during their preschool years were more than four times as likely to become obese adults compared to their normal-weight peers [6]. Furthermore, another piece of evidence from a previous study has shown that overweight children have at least twice the risk of remaining overweight into their adult life compared to children in the healthy weight range [7]. Due to short-term and long-term impacts on health, including predisposition to diabetes and cardiovascular abnormalities, childhood obesity should be viewed as a serious concern for public health [8]. Moreover, the increase in the prevalence of childhood obesity and the tendency to become obese adults at a later age [9], highlighting this period is critical for preventive action [10]. Therefore, considering public health priority and currently available data on the nutritional status of preschool children, a comprehensive and effective weight-related behavioural intervention programme is urgently needed in Malaysia to reduce the risk of unhealthy weight, especially childhood obesity.

The preschool years are a vital time for establishing healthy lifestyle behaviours [11], and World Health Organization has highlighted it as a critical period for obesity prevention [12]. Systematic reviews of obesity prevention studies also suggested that preschool- and school-based interventions are useful in reducing the prevalence of childhood obesity [13, 14]. Preschool settings pose a realistic target for the health-related behaviour change intervention. The characteristics of the preschool, including policies and practices regarding dietary intake and physical activity, can significantly influence children’s healthy behaviour [15]. Moreover, preschools represent an ideal setting to address social inequalities because they provide access to the population and generally have the necessary facilities, curriculum, environment, and personnel to promote physical activity and healthy eating [16, 17].

Furthermore, preschool plays an essential role in facilitating or delivering health-related behaviour change intervention programmes. These include the organisational structure and the high level of trust that children and parents attach to preschool staff [18]. Also, preschool is a crucial stage for early education in Malaysian children under 18 years. The preschool years (aged 4 to 6 years) are the first stage of transition before starting primary school (aged 7 to 12 years), which is the compulsory requirement for education in Malaysia. In addition, declining physical activity, deterioration of dietary behaviours, and increasing recreational screen-time, increase during the early teenage years [17, 19]. Thus, the preschool represents an opportunity for delivering and exposing healthy lifestyle interventions before starting primary school. Besides that, the preschool setting is an arena where repeated exposure of education intervention can be implemented systematically and also can be a potential setting for influencing children’s lifestyles at an early age [20]. Therefore, weight-related behavioural interventions are particularly important in improving the physical activity and dietary behaviours of preschool children.

Moreover, children who participate in a lifestyle intervention at an earlier age (4 to 7 years) have greater weight loss over five years than those participating in the intervention at an older age (>11 years) [11]. Thus, weight-related behavioural interventions should start at an early age [9], and many studies have revealed greater success for programmes targeting the early-aged group [16]. During early childhood, lifestyle behaviours that promote obesity are just being learned, and it is easier to establish new behaviours than to change the existing ones [21]. Furthermore, health behaviours become more difficult to change with age and tend to track into adulthood but are quite malleable in the early years [22]. Once childhood obesity is established, it is difficult to reverse through interventions [13, 23]. Therefore, early childhood is an opportune time to intervene, and involving parents in interventions appears to be crucial [22].

The use of Information and Communication Technology (ICT) in adolescent and adult age groups has increased in recent years, especially in Malaysia. A report by the Department of Statistics Malaysia on ICT use and access by individuals and households survey has shown that the percentage of individuals in Malaysia aged 15 years and above that used the internet was 81.2% in 2018, which increased by 1.1% points as compared to 80.1% in 2017 [24]. In terms of ICT access by households, the percentage of households’ access to the internet increased by 1.3% points to 87.0% in 2018 as compared to 85.7% in 2017. The percentage of households’ access to mobile phones also increased by 0.1% points to 98.2% in 2018 as compared to 98.1% in 2017 [24]. The high ICT used and accessed by individuals and households in Malaysia highlights the importance of the web-based approach for effective home-based intervention programmes. In addition, it is well understood that online education provides many benefits for teaching and learning environments. Distributing information and materials online increases the availability of the intervention, making it easy for parents to find the information at their convenient time [20]. To our knowledge, there are limited intervention studies that integrate classroom activities and an interactive Web-based programme targeting preschool child-parent dyads, especially in Malaysia.

A finding from the recent systematic review revealed that most health-related interventions were concentrated in the primary and secondary school setting [25]. On the other hand, few intervention studies were conducted in the preschool or home settings. Thereby, the evidence for weight-related behavioural intervention primarily done in the preschool setting was relatively weak because of the few studies published [11, 14, 25]. Notably, most intervention studies to prevent childhood obesity in preschool settings were exclusively done in high-income developed countries [25]. Few were done in upper-middle-income developing countries. The systematic review study also suggested that the preschool-based randomised controlled trial combined diet and physical activity has been shown to have beneficial intervention effects [25]. However, all the preschool-based randomised controlled trials in the study were done in the United States of America (USA), which involved low-income or ethnic minority populations. Another systematic review study found that more than half of the health-related behaviour change intervention studies were conducted in the USA [26]. Most studies were done in developed countries, making it challenging to generalise the results globally. Considering the increasing trend of childhood obesity prevalence in developing countries, the lack of documented interventions is a serious limitation of the existing literature.

Interventions targeting multiple settings might hold the most promise in reducing the risk of unhealthy nutritional status, especially childhood obesity. The home environment is recognised as a strong influence on the health-related behaviours of children. Most school-based studies that included a home setting reported beneficial intervention effects [25]. However, evidence to support the effectiveness of the combination of preschool- and home-based intervention on weight-related behavioural intervention among children was limited [25]. Even though there are limitations to the available data, the importance of the home setting for weight-related behavioural intervention among children should not be discounted. Thus, based on current literature, more research with rigorous evaluation primarily done in preschool settings in combinations with home settings is greatly needed to support the development of comprehensive recommendations for weight-related behavioural intervention. Future research should expand on the existing evidence in preschool and home settings with specific attention to the implementation of studies in developing countries, especially in Malaysia, are warranted.

### Objectives

The general aim of this study is to evaluate the efficacy of the 3-month *i-MaCHeL* programme, a web-based, theory-driven intervention to change weight-related behaviour in preschool child-parent dyads. The primary objective is to compare the differences in BMI z-score between the intervention and control groups of preschool children at 3 months and 9 months’ post-baseline. The secondary objectives are: 1) to compare the difference in dietary intake, physical activity, screen time duration, and health-related quality of life between the intervention and control groups of preschool children at 3 months and 9 months’ post-baseline and; 2) to compare the difference in parental self-efficacy, parental role modelling, and parental policies between the intervention and control groups of parents at 3 months and 9 months’ post-baseline.

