### Sample size

The sample size is calculated for the primary outcome, BMI z-score. The sample size for individual randomisation of the present study is based on Formula 1 [29]. The values used in the sample size calculation are based on the BMI z-score data from Ahmad et al. (2018) [30] study, which is 1.95±0.45 and 2.09±0.35 for the treatment and control groups, respectively. Based on Formula 1, a calculated sample size required for each group arm is 131 child-parent dyads. It is calculated that, with at least 80% power to identify a small to medium effect size [31] at the 5% significance level, the present study needs a total of 262 child-parent dyads for the two-group arm.

$${}^{n}Individual\_Binary=\frac{{\left(z_{1-\frac{\alpha }{2}}+z_{1-\beta }\right)}^{2}[\sigma_{trt}^{2}+\frac{\sigma_{con}^{2}}{r}]}{\Delta^{2}}$$
(1)

**where**, $r=\frac{n_{con}}{\sigma_{con}},\Delta =\mu_{trt}-\mu_{con}$

*μ*_*trt*_ = Mean in treatment group = 1.95

*μ*_*con*_ = Mean in control group = 2.09

*σ*_*trt*_ = SD. in treatment group = 0.45

*σ*_*con*_ = SD. in control group = 0.35

*z* = Critical *z* value for a given Alpa (*α*) = 0.05 (two − sided) and Beta (*β*) = 0.2 with the value of $z_{1-\frac{\alpha }{2}}$ = 1.96 and *z*_1−*β*_ = 0.84

*r* = Ratio of the two sample sizes = 1/1

An adjustment using the design effect (DE) is made for the calculated sample size to allow for the design structure (due to the cluster sampling method), which results in larger sample sizes [32]. Taking into account unequal cluster size [10], assume the mean cluster size of 38 child-parent dyads will be recruited per preschool. Based on the Formula 2 [32, 33], given that the number of individuals per cluster (*n*) in the present study is 38 child-parent dyads and the Intra-cluster correlation coefficient (*ρ*) from the previous studies is 0.01 [18, 34], the calculated design effect of the present study is 1.37.

Designeffect(DE)=1+(n–1)ρ
(2)

By considering the design effect is 1.37 and the sample size required for each group arm (^*n*^Individual_Binary) is 131 (see Formula 3), the total sample size of the individual randomisation is further increased from 262 to 360 child-parent dyads.

$$({}^{n}Individual\_Binary)\times Design\;effect\times 2$$
(3)

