### Data collection

#### Outcomes

The primary outcome measure is the BMI z-score. The secondary outcomes measures are children’s dietary intake, physical activity, screen time duration, health-related quality of life, parental self-efficacy, parental role modelling, and parental policies. All the outcomes will be assessed at baseline, immediately following the intervention completion (3 months’ post-baseline), and at 6 months’ follow-up (9 months’ post-baseline) using anthropometric measurements (weight and height), three-day food record, and validated questionnaires. The participant’s timeline is presented in Table 2.

**Table 2 pone.0276843.t002:** Schedule of enrolment, interventions, and assessments in the *i-MaCHeL* programme. SPIRIT table as recommended by the 2013 SPIRIT Statement.

Activity & assessment	Study period								
	Enrolment	Allocation	Baseline	3-month intervention period			3-month post-baseline	6-month follow-up	Close-out
Timepoint	Oct 21—Mar 22	Apr 22	Month 0	Month 1	Month 2	Month 3	Month 3	Month 9	Jan 23

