### Statistical methods

Differences in changes over time between the intervention and comparison groups will be assessed for each outcome. General linear model repeated measure analysis will be used to determine differences between groups over time (baseline, 3-month, and 9-month) with adjustment for potential covariates. Intention-to-treat (ITT) principles will be applied for parametric data. All participants will be analysed in both intervention and control groups regardless of whether they attended all data collection time points or completed the intervention [22]. The intention-to-treat principle is useful to preserve the sample size by including all randomised respondents regardless of noncompliance or withdrawal. The principle will be used to lower the probability of reduced statistical power due to the dropouts excluded from the final analysis.

Descriptive statistics (percentages or mean ± SD) will be calculated to describe participants’ sociodemographic characteristics and scores for each outcome measured by treatment and control groups. Repeated measures Analysis of Covariance (ANCOVA) will be performed to determine significant differences between groups at the 3- and 9-month surveys. The measures analyses will be controlled for covariate variables known to influence the outcome measures (child gender, parent education level, parent age, and parent income) [22]. The significance level will be set at ≤ 0.05. Analyses will be performed using Statistical Product and Service Solutions (SPSS; version 25.0; IBM, Armonk, NY, USA).

As randomisation will be at the school (cluster) level, the primary analysis will be adjusted for the clustering effect and the baseline value of the outcomes [63, 64]. Subgroup analysis will be performed to determine the direction of intervention effects by socioeconomic status, sex, and weight status. Where appropriate, multiple imputation methods will be used to account for missing data [18].

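### The primary objective compares BMI z-score at both 3 and 9 months at an undivided 0.05, with no deciding visit, order or success rule, while the sample size covers one comparison

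*Protocol article*

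**What the plan says.** Objectives gives one primary objective with two time points: to "compare the differences in BMI z-score between the intervention and control groups of preschool children at 3 months and 9 months" after baseline. Neither visit is ranked above the other.

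Outcomes states "The primary outcome measure is the BMI z-score" and attaches no time point to it. All outcomes are assessed at baseline and at both later visits.

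Statistical methods describes two analyses. First, "General linear model repeated measure analysis will be used to determine differences between groups over time (baseline, 3-month, and 9-month"), with covariate adjustment. Then a repeated-measures ANCOVA "will be performed to determine significant differences between groups at the 3- and 9-month surveys". One level covers everything: "The significance level will be set at ≤ 0.05". The same section adds that "the primary analysis will be adjusted for the clustering effect and the baseline value of the outcomes", without saying which test or visit that primary analysis refers to.

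Sample size is worked for BMI z-score "with at least 80% power to identify a small to medium effect size" at the 5% level. It uses a single pair of means (1.95 and 2.09) and two-sided z values of 1.96 and 0.84. No visit is named there either.

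**The concern.** There is one efficacy question, two comparisons that could answer it, and one level applied to each without division. The article intends a single verdict: Significance and outlook discusses possible adoption by the education ministry if the programme proves efficacious. It does not say which result would count as efficacious.

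Two things follow. If a significant result at either visit may be reported as efficacy, the 5% level assumed in the sample size does not describe that claim. And if the visits disagree, the trial has no defined primary conclusion. An effect at 3 months that fades by 9 months is a plausible outcome for a 3-month programme, and the choice of which visit to stress could then be made after the results are seen.

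**Working it through.** **The plan's own sample size.** Inputs from Sample size: SDs 0.45 and 0.35, difference 2.09 − 1.95 = 0.14, z = 1.96 and 0.84, ratio 1:1.

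- Per arm: (1.96 + 0.84)² × (0.45² + 0.35²) / 0.14² = 7.84 × 0.325 / 0.0196 = 130.0. With unrounded z values it is 130.15, which rounds up to the stated 131.
- Design effect: 1 + (38 − 1) × 0.01 = 1.37.
- Total: 131 × 1.37 × 2 = 358.9 (stated 360).
- After 20% loss: 360 / 0.8 = 450 (stated 460).

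The plan's figures are thus reproduced to within about 3%. They correspond to one comparison at two-sided 5%, with no allowance for a second.

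**Error rate with two visits.** Let Z₁ and Z₂ be the test statistics at 3 and 9 months, with no true effect at either, each tested at |Z| > 1.96, and with correlation r between them. The documents do not give r, so it is an assumption and a range is shown. Two measurements of BMI z-score on the same children six months apart should be clearly correlated, so 0.5 to 0.9 is taken as the working range.

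- Either visit suffices: 1 − P(|Z₁| < 1.96 and |Z₂| < 1.96), from the bivariate normal distribution.
- Both visits required: 5% + 5% − the either-visit rate.
- False claim of benefit under the either-visit rule: about half the two-sided rate, by symmetry.

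| r | Either visit, two-sided | Either visit, false benefit | Both visits required, two-sided |
|---|---|---|---|
| 0 (independent) | 9.75% | 4.9% | 0.25% |
| 0.5 | 9.07% | 4.5% | 0.93% |
| 0.7 | 8.35% | 4.2% | 1.65% |
| 0.8 | 7.81% | 3.9% | 2.19% |
| 0.9 | 7.04% | 3.5% | 2.96% |
| 0.95 | 6.46% | 3.2% | 3.54% |
| 0.99 | 5.66% | 2.8% | 4.34% |

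For independent tests the either-visit rate is 1 − 0.95² = 9.75%.

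**Check at the trial's cluster count.** With 12 simulated cluster means, 6 per arm, and t tests on 10 degrees of freedom, the either-visit rate was 9.2%, 8.5%, 8.0% and 7.3% at r = 0.5, 0.7, 0.8 and 0.9. The small number of preschools barely changes the result.

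**If a joint test is a gate.** In the same simulation, a joint test of the two visits at 5% had to be significant before either visit was read. The chance of any false visit claim fell to 3.8% at r = 0.5 and 3.0% at r = 0.9.

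The text is therefore compatible with rules whose error, over r = 0.5 to 0.9, runs from about 1% to about 9%.

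**The case against.** The strongest reply is that no either-visit rule is written down. Statistical methods opens with differences in change over time, fits one repeated-measures model and speaks of the primary analysis in the singular. The visit comparisons may be follow-up contrasts within that model. If the over-time test were primary or a gate, the error with no effect at either visit would be at most 5%. If both visits were required, it would be about 1% to 3%. This stands: a reader might infer that the trial's false-positive rate simply is 7% to 9%, and the document does not support that as a statement of fact.

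A reader might also infer that the over-time test is a third route to success and raises the error further. That is not supported either. The article gives the test no such role, and as a gate it would lower the error.

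The two-sided rate also counts false findings of harm. For a false claim of benefit, the relevant comparison is 3.5% to 4.5% against 2.5%. This stands too.

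Finally, testing order and division of alpha are often left to an analysis plan, and this article condenses a fuller protocol. That reply succeeds only in part. The primary objective, the primary outcome, the significance level and the basis of the sample size are all stated here, and they do not fit together: two primary comparisons are named and one is sized.

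**Conclusion.** The concern holds in conditional form. The article names two primary comparisons, applies an undivided 0.05, sizes one comparison and gives no rule to connect them. If significance at either visit counts as efficacy, the two-sided false-positive rate is about 7% to 9%. That figure rests on an assumed correlation of 0.9 down to 0.5 and on each single test holding its own 5%. The rate exceeds 5% for any correlation below 1 and cannot exceed 9.75% for tests that are independent or positively correlated.

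The undefined conclusion when the visits disagree depends on no assumption. The matter should be settled, but it does not undermine the design, and it can be corrected without recruiting more dyads.

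**What to change.** Before outcomes are compared by group, state one decision rule in Objectives and repeat it in Statistical methods. Either of these holds two-sided 5%:

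- **Fixed sequence.** Test the 3-month difference at two-sided 5%. Test 9 months at the same level only if 3 months is significant.
- **Single primary visit.** Name one visit as primary and report the other as secondary.

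In both cases make the group-by-time test secondary, and state in Sample size that the calculation refers to the comparison that decides, or that comes first in the sequence. The wording cost is a sentence in each of these places, and the total stays at 460. The real cost is that an effect seen only at the non-primary or later-ordered visit becomes descriptive.

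Dividing alpha as 0.025 per visit would also control the error, but not for free. The requirement per arm rises from 131 to 158, the total after the design effect to 2 × 158 × 1.37 = 433, and after 20% loss to 433 / 0.8 = 542 (each rounded up).
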